### Nested process evaluation

A nested process evaluation examined programme theory, programme implementation and how NERS was received, facilitating an in-depth understanding of the views of providers and users, as well as interpretation of outcome effects [51]. Guided by the framework proposed by Steckler and Linnan [52], the process evaluation explored diffusion of the national policy across local contexts, fidelity and dose of implementation, patient experiences, programme reach and recruitment. The process evaluation adopted a pluralistic multi method approach involving triangulation [53] of multiple perspectives and methods (Table 2). All analysis will be conducted prior to any knowledge of outcome effects to guard against interpretation bias

**Table 2 T2:** Process evaluation methods

Participants	Methods	Areas for investigation
Welsh Assembly Government representatives (n = 3)	Group interviews and email/telephone communication	Programme theory Programme diffusion and barriers and facilitators to implementation

General Practices (n = 9)	Group interviews with primary care clinicians (GPs, practice nurses; practice managers)	Recruitment Uptake and reach

All exercise co-ordinators (n = 12)	One to one telephone interviews	Fidelity and dose Programme diffusion and barriers and facilitators to implementation Recruitment Uptake and reach Trial experience and implementation

All exercise professionals (n = 38)	One to one telephone interviews	Fidelity and dose Patient experiences - perceived impact and processes of change Uptake and reach Trial experience and implementation

Patient interviews (n = 32 within 6 centres)	Group and one to one interviews with patients at varying stages of the scheme	Patient experiences - perceived impact and processes of change

Exercise professionals (n = 23)	Recordings of at least one first consultation for all exercise professional and coding using Behaviour Change Counselling Index (BECCI; (Lane, Huws-Thomas et al. 2005).	Fidelity

Routine monitoring data (1080 patients)	Secondary analyses	Fidelity and dose Uptake and reach

In order to elicit programme theory and provide a framework for implementation checks, a programme logic model was developed through examination of scheme protocols and telephone and email contact with policy representatives. Quantitative assessments of programme implementation in terms of fidelity (i.e. consistency with programme theory) and dose delivered, draws on a combination of self reports from professionals and coordinator telephone interviews, as well as routine monitoring data and structured observation of tape recorded consultations. Exercise professionals were supplied with recording equipment and asked to provide recordings for at least one initial consultation, rated by two independent coders for fidelity to motivational interviewing principles using the Behaviour Change Counselling Index (BECCI); [54]. Programme uptake and reach are quantitatively assessed using routine monitoring data.

Experiences of diffusing the national policy into local contexts were explored through qualitative semi-structured telephone interviews with policy representatives and all local area coordinators. All exercise professionals were invited to participate in one to one telephone interviews exploring issues including experiences of implementing the scheme and perceived patient responses to the programme. In order to incorporate patients' perspectives on the programme, six case study centres were sampled purposively to represent a range of geographical areas and levels of deprivation and two members of the research team visited each centre. Patients attending the centre on the day of the visit were informed in advance of the researchers' attendance, and were invited to participate in group or one to one semi-structured interviews immediately after classes finished. In addition, GPs, practice nurses and practice managers referring patients to the scheme were interviewed, exploring influences on trial and scheme recruitment. Nine group interviews were conducted across areas, practice size and level of referral.

### Nested economic evaluation

The nested economic evaluation [55-57] took a public sector, multi agency perspective, spanning the Welsh Assembly Government (WAG), local government and the NHS. It costed the national exercise referral programme using WAG and local authority exercise programme budgets. In addition, telephone interviews with all principal leisure centre managers ascertained any additional expenditure incurred by local authorities in establishing and running NERS. Similarly telephone interviews ascertained the costs to WAG of establishing and coordinating the Scheme. The questionnaire data recorded trial participant primary and secondary care health service use, costed using national unit costs [58,59]. With this, we will conduct a primary cost utility analysis to calculate the cost per QALY of NERS. We will undertake sensitivity analysis to explore what happens when we add in the cost of a specific GP consultation to facilitate referral onto NERS, and the effect of participants paying £1 or £2 per exercise session. Sensitivity analysis will be particularly important in the application of economic evaluation methods to a large pragmatic public health trial [60]. We will undertake subgroup analysis to investigate how age, gender, adherence and main reason for referral e.g. CHD risk or mental health problems, affects our estimates of the cost per QALY of NERS. We will use EQ-5D as our measure of utility to generate a cost per QALY and Cost Effectiveness Acceptability Curve (CEAC) for comparison with the NICE ceiling of £30,000 [61].

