## Methods and Design

### Study Design

The evaluation study comprised three key components. In order to evaluate the overall effectiveness of the intervention, a randomised controlled design was employed. Mixed methodology RCTs have the potential to provide unbiased estimates of the effectiveness of interventions as well as identifying contextual influences on intervention delivery [27]. A nested process evaluation therefore examined how the initiative was implemented, gained a more in-depth understanding of the views of providers and users, and facilitated interpretation of outcome effects. A nested economic evaluation was also undertaken in the form of a cost utility analysis which measured costs and benefits from a public sector multi-agency perspective, with results expressed as an incremental cost per quality adjusted life year (QALY) gained. In this way, the evaluation not only addresses the question, 'Does it work?', but also considers 'What works?', 'For whom?' 'Under what circumstances?' and 'At what cost?'[28]. A summary of the study design is presented in Figure 1.

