#### Cost utility at 6 and 12 months

The primary outcome measure for the economic analysis will be the quality adjusted life year (QALY). This is a measure of health utility. This is calculated by 'weighting' each period of follow-up time by the value corresponding to the health-related quality of life reported by study participants [38,39]. Health related quality of life was assessed using the EQ-5D questionnaire collected at 6 and 12 months [40]. The EQ-5D is a validated generic health-related preference-based measure made up of five items covering mobility, self-care, usual activity, pain, anxiety and depression, each with three levels of severity (no problems, some problems, a lot of problems). EQ-5D is supported by National Institute for Health and Clinical Excellence (NICE). The Short Form 12 Health Survey (SF-12) assessed general health status at 6 and 12 months in terms of physical and mental functioning [41].

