### Data analysis

The primary analysis of the primary outcome is a regression model with the stratification variables (gender/LHB area), age group (16-44, 45-59, 60+) and baseline activity level (GPPAQ) included as covariates. In the event that the primary outcome has a highly skewed or bimodal distribution, it will be recoded as a five level ordinal variable, and ordinal regression used in the primary and secondary analyses. These analyses will be conducted on an intention-to-treat basis, in which each participant is coded according to the treatment condition to which they were randomised. A secondary analysis of the primary outcome repeats the primary analysis, but excluding baseline activity level as a covariate. For the primary outcome only, the primary and secondary analyses will be conducted (i) for all participants completing the 7-DAY PAR and (ii) with the addition of multiply imputed values of the primary outcome for those who did not complete the 7-DAY PAR but who did complete either the Baecke or GPPAQ instruments at 12-month follow-up.

The primary analysis for the primary outcome, and for imputed values of 7-DAY PAR, is repeated to conduct sub-group analyses for each of the following variables: gender, age group (16-44, 45-59, 60+), referral reason (mental health only, CHD only, or combination of CHD and mental health), Welsh Index of Multiple Deprivation tertile, fidelity of programme implementation in LHB area (high/low). In each case, the statistical significance of sub-group effects is assessed by including an interaction term in separate models for each respective sub-group variable, with each model also including the main effect for the respective sub-group variable. An analysis to identify whether outcomes vary in terms of exposure to the programme replaces the binary intervention group variable with the three level programme attendance variable.

The analyses described in the preceding two paragraphs are also conducted for the secondary outcome. However, the primary analysis for the secondary outcome (HADS anxiety and depression scales) is conducted only among participants referred for mental health only or a combination of mental health and CHD reasons. The analyses of the secondary outcome among all participants is secondary to this analysis.

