### Recruitment

Trial recruitment occurred in 12 of the 13 areas, with one area failing to start a scheme during the trial period. Between July 2007 and October 2008, 4,779 health professional referrals were received by the evaluation team. Of these, 1,493 were not eligible for the trial and their referral forms were forwarded to the ECs for processing directly onto the scheme. The remaining 3,286 were sent full informed consent information and a baseline questionnaire. In total 2,160 patients were recruited to the trial, with 890 not responding and 236 not consenting to participate in the trial.

Respondents ranged between 16 and 88 years old, with a mean age of 52 (SD 14.7) and the vast majority classed themselves as white (96%). Whilst, measures of area deprivation ranged from 2.3 to 81.0 with a mean of 22.6 (SD 14.6). Table 3 shows that the majority were referred for CHD risk factors on their own (72%) or in combination with mental health conditions (24%), with only 4% referred solely for mental health reasons. Those recruited were most likely to be female (66%), to be married or with a partner (61%) and there was a fairly equal split between those employed (31%) and retired (32%). Finally, whilst the majority referred onto the scheme classified themselves as either inactive or moderately inactive (74%), 24% defined themselves as either active or moderately active.

**Table 3 T3:** Baseline measures for recruited sample

Measure	% (N)
**Reasons for referral** CHD CHD and Mental Health Mental Health	72.2 (1,559) 24.2 (522) 3.7 (79)

**Gender** Female Male	65.5 (1,415) 34.5 (745)
**GPPAQ** Inactive Moderately inactive Moderately active Active Missing	58.6 (1,266) 15.3 (330) 15.8 (342) 8.2 (176) 2.1 (46)
**Employment** Retired Employed Housework Other Seeking work Student Missing	31.9 (666) 30.8 (646) 19.1 (413) 13.1 (282) 3.2 (69) 1.9 (40) 2.0 (34)
**Education** > Minimum education	52.1 (1,127)
**Marital status** Married/Partner Single Divorced/Separated Widowed Missing	61.4 (1,326) 17.8 (384) 13.6 (293) 6.0 (129) 1.3 (28)

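### Economic sub-group effects are to be judged on cost per QALY, a ratio that cannot be validly differenced between sub-groups; net benefit with an interaction term would serve

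*Protocol article*

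**What the plan says.** All places are in the protocol article.

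- *Study Design* sets the form of the economic result: "results expressed as an incremental cost per quality adjusted life year (QALY) gained".
- *Nested economic evaluation* carries that quantity into the sub-groups: "We will undertake subgroup analysis to investigate how age, gender, adherence and main reason for referral" "affects our estimates of the cost per QALY of NERS", with the text between these two runs giving CHD risk and mental health problems as examples of referral reasons.
- The next sentence of that section plans a cost per QALY and a "Cost Effectiveness Acceptability Curve (CEAC) for comparison with the NICE ceiling of £30,000". It does not say whether the curve is for the whole sample only or is repeated by sub-group.
- *Data analysis* treats sub-groups differently for the effectiveness outcomes: "the statistical significance of sub-group effects is assessed by including an interaction term in separate models for each respective sub-group variable".
- Table 3 gives the group sizes by referral reason as 1,559 (CHD), 522 (CHD and mental health) and 79 (mental health only), and by gender as 1,415 women and 745 men.

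**The concern.** The sub-group question is about a difference: does the scheme give better value in one kind of patient than in another? A ratio of cost difference to QALY difference answers that poorly, for three reasons.

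1. It has no value when the QALY difference is zero, and becomes very large on either side of zero.
2. A negative ratio is ambiguous. It arises both when the scheme costs less and does more and when it costs more and does less.
3. Two sub-group ratios cannot be subtracted or ranked to give a meaningful effect of the sub-group variable.

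The article expects a small denominator. Its Background describes the one earlier trial with a thorough economic evaluation as finding exercise costlier and only a little more effective than advice.

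At stake is the stated aim of learning for whom the scheme works and at what cost. A sub-group could appear to be poor value, or produce a figure with no clear meaning, because its QALY estimate happened to fall below zero.

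**Working it through.** **No figure to reproduce.** The article states no expected QALY gain, QALY SD, cost difference or economic power. Its power figures concern weekly activity and do not bear on this point.

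**Step 1: the ratio is ambiguous (illustrative figures).**
- Cost +£400, QALY −0.02: ratio = 400 / (−0.02) = −£20,000. Net benefit at £30,000 = 30,000 × (−0.02) − 400 = −£1,000.
- Cost −£400, QALY +0.02: ratio = −400 / 0.02 = −£20,000. Net benefit = 30,000 × 0.02 + 400 = +£1,000.

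The ratio is the same and the conclusions are opposite. Net benefit separates them.

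**Step 2: how often a sub-group QALY estimate takes the wrong sign.**

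From Table 3: the sub-group sizes N. Assumed: equal arms, 75% with QALY data, the same true gain in every sub-group, gain 0.01 to 0.03, SD 0.10 to 0.30.

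Formulas: n per arm = 0.75 × N / 2; SE = SD × √(2/n); chance of an estimate below zero = Φ(−gain / SE).

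Worked case, mental health only, gain 0.02, SD 0.20: n = 0.75 × 79 / 2 = 29.6; SE = 0.20 × √(2/29.6) = 0.052; Φ(−0.02/0.052) = Φ(−0.385) = 35%.

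| Sub-group | N | gain 0.03, SD 0.10 | gain 0.02, SD 0.10 | gain 0.02, SD 0.20 | gain 0.01, SD 0.30 |
|---|---|---|---|---|---|
| CHD only | 1,559 | <0.1% | <0.1% | 4% | 28% |
| CHD and mental health | 522 | 0.1% | 2% | 16% | 37% |
| Mental health only | 79 | 12% | 22% | 35% | 45% |
| Women | 1,415 | <0.1% | 0.1% | 5% | 29% |
| Men | 745 | <0.1% | 1% | 12% | 35% |

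The first and last columns of percentages are the best and worst corners of the grid.

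**Step 3: spread of the ratio when nothing differs between sub-groups.** Further assumptions: true cost difference £400 (SD £1,500), gain 0.02, cost and QALY independent, so the true ratio is 400 / 0.02 = £20,000 everywhere. Simulated 95% ranges:
- CHD only: £9,700 to £49,700 at SD 0.10; −£89,000 to £151,000 at SD 0.20.
- Mental health only: −£197,000 to £226,000 at SD 0.10; −£132,000 to £131,000 at SD 0.20.

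So the ratio is usable in the largest referral group at the smaller SD, breaks down there at the larger one, and is uninformative in the group of 79 under both. The range for the 79 is not wider at SD 0.20 than at 0.10, although the data are noisier. That shows the spread of a ratio does not track precision once the denominator straddles zero.

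**Step 4: the same data as net benefit.** The true value is 30,000 × 0.02 − 400 = £200. SE = √[(4 / (0.75N)) × ((30,000 × SD)² + 1,500²)]. At SD 0.20 this gives about £360 for CHD only and about £1,610 for the 79. It is always finite, and its difference between groups has an ordinary standard error, but it is still very imprecise for the 79.

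**The case against.** The strongest reply has four parts.

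*The article does not say that point ratios will be ranked, subtracted or tested.* True, and nobody should infer that it does. But it does name the quantity whose variation across sub-groups is to be studied, and that quantity is the ratio.

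*An acceptability curve is already planned, and it behaves well near a zero QALY difference.* This also stands: the curve is the probability of positive net benefit at each threshold. However, the article does not attach it to the sub-groups, and separate curves side by side would still not estimate the difference between groups.

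*Model details belong in a fuller plan that is not shown.* Agreed for the bootstrap, the regression form and the handling of dominance. The choice of metric is not left to that plan; it is stated here. The interaction terms in *Data analysis* apply to effectiveness outcomes, so their absence from the economic section is a contrast and not a contradiction.

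*Net benefit does not cure noise.* Correct. With the Step 4 assumptions at SD 0.20, the estimated net benefit has the wrong sign with probability Φ(−200/1,610) = 45% for the 79 and Φ(−200/360) = 29% for CHD only. The gain is an interpretable difference with a valid interval, not more precision.

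A reader might go further and infer that sub-group differences in cost per QALY will be mostly noise. The documents do not support that. They give no QALY gain or SD, and in the larger groups the sign risk falls to almost nothing under favourable inputs. The high figures depend heavily on the group of 79, and the economic section does not commit to analysing that group separately: its examples of referral reason can be read as two categories.

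**Conclusion.** The point holds in limited form. Cost per QALY is a poor scale for comparing sub-groups: it is undefined at a zero QALY difference, ambiguous in sign and not validly differenced. The planned curve does not fill that gap as written.

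How often this would matter rests on assumed inputs (gain 0.01 to 0.03, SD 0.10 to 0.30, 75% follow-up, equal arms, one common true gain). On that grid, a wrong-signed QALY difference is a material risk throughout for mental health only, and ranges from negligible to substantial in the other groups. The overall cost per QALY is not in question. Minor to moderate severity.

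**What to change.** In the economic analysis, for the sub-groups defined at baseline (age, gender, referral reason):

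- Assess differences on incremental net monetary benefit at the £30,000 already named, and across the range of thresholds used for the acceptability curve.
- Estimate them in a regression with randomised arm, sub-group and their interaction, and report the between-group difference with a bootstrap or robust interval.
- Add an acceptability curve for each sub-group.
- Treat the 79 participants referred for mental health only as descriptive if they are shown separately.
- Keep the overall cost per QALY as planned.

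Adherence is left out of this list because attendance arises after randomisation and has no randomised comparator; it needs separate treatment.

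The cost is a few sentences in the economic plan and a few lines of code, with no new data. The downside is that net benefit is less familiar to policy readers, and small sub-groups stay imprecise on any scale.

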### Recruitment

Trial recruitment occurred in 12 of the 13 areas, with one area failing to start a scheme during the trial period. Between July 2007 and October 2008, 4,779 health professional referrals were received by the evaluation team. Of these, 1,493 were not eligible for the trial and their referral forms were forwarded to the ECs for processing directly onto the scheme. The remaining 3,286 were sent full informed consent information and a baseline questionnaire. In total 2,160 patients were recruited to the trial, with 890 not responding and 236 not consenting to participate in the trial.

Respondents ranged between 16 and 88 years old, with a mean age of 52 (SD 14.7) and the vast majority classed themselves as white (96%). Whilst, measures of area deprivation ranged from 2.3 to 81.0 with a mean of 22.6 (SD 14.6). Table 3 shows that the majority were referred for CHD risk factors on their own (72%) or in combination with mental health conditions (24%), with only 4% referred solely for mental health reasons. Those recruited were most likely to be female (66%), to be married or with a partner (61%) and there was a fairly equal split between those employed (31%) and retired (32%). Finally, whilst the majority referred onto the scheme classified themselves as either inactive or moderately inactive (74%), 24% defined themselves as either active or moderately active.

**Table 3 T3:** Baseline measures for recruited sample

Measure	% (N)
**Reasons for referral** CHD CHD and Mental Health Mental Health	72.2 (1,559) 24.2 (522) 3.7 (79)

**Gender** Female Male	65.5 (1,415) 34.5 (745)
**GPPAQ** Inactive Moderately inactive Moderately active Active Missing	58.6 (1,266) 15.3 (330) 15.8 (342) 8.2 (176) 2.1 (46)
**Employment** Retired Employed Housework Other Seeking work Student Missing	31.9 (666) 30.8 (646) 19.1 (413) 13.1 (282) 3.2 (69) 1.9 (40) 2.0 (34)
**Education** > Minimum education	52.1 (1,127)
**Marital status** Married/Partner Single Divorced/Separated Widowed Missing	61.4 (1,326) 17.8 (384) 13.6 (293) 6.0 (129) 1.3 (28)

## Discussion

Previous attempts to facilitate rigorous evaluations of exercise referral schemes have been hampered by policy and practice constraints [25,26]. Existing studies meanwhile, have suffered from a number of methodological shortcomings, not least significant barriers to recruitment [6] and a lack of understanding of the causal and implementation process of ERS means that we still do not know what types of ERS have worked, why, for whom, in what circumstances and at what cost [28]. To address these shortcomings, this study included early and sustained collaboration with policy and practice partners, adopted an innovative approach to trial recruitment and included comprehensive nested process and economic evaluations. Such strategies will not only facilitate rigorous evidence on the effectiveness of the national exercise referral scheme but provide examples of good practice for the design and conduct of trials of similar policy interventions.

### Establishing effective recruitment strategies

In Wales, the NERS was introduced within a RCT design in the context of the termination of pre-existing local schemes. This was particularly challenging, as a significant barrier to facilitating rigorous designs has been professional reluctance to refer into trials when there is a perception of change or withdrawal of service, regardless of the evidence base for the effectiveness of that service [25]. Establishing effective recruitment strategies was further complicated by a reliance on primary care clinicians as the main source of referral into the scheme. It has been argued that such clinicians are well placed to promote increased physical activity [62,63]. However, previous studies have found that physical activity promotion was not a priority during routine consultations [42,64], that there is a lack of consensus in how clinicians perceive their role in changing patients' behaviour and that patients are frequently referred in an unsystematic way [42,65].

Despite this, the trial achieved referrals from 12 of the 13 implementation areas (with one area failing to start the scheme) and a high referral rate from clinicians. This may be in part a function of the size of the scheme being evaluated, but was also facilitated by a number of strategies employed in the conduct of this study. This included briefing sessions for professional stakeholders by the evaluation and national policy team at an early stage to address concerns and promote the evaluation. At the local level, the provision of Exercise Coordinators who were able to promote the trial with clinicians also facilitated professional participation. Particularly important was the fact that trial recruitment was undertaken by the evaluation team after clinicians had provided basic information to patients. This placed a low research burden on health professionals who promoted but did not recruit to the trial.

Examining characteristics of those recruited to the trial highlights the greatest proportion were referred for CHD risk, that there were a larger number of females and a significant minority who classified themselves as active or moderately active. Although the scheme was targeted at sedentary individuals, this latter finding reflects the pragmatic nature of the trial which placed minimal control on the implementation of the scheme other than randomisation. Results are therefore likely to be highly reproducible and have high external validity. This is particularly important given previous criticisms of RCTs of ERS that what is gained in internal validity is often at the expense of external validity [66]. Influences on NERS referral processes and the acceptability of trial recruitment strategies will be assessed within the nested process evaluation which will explore influences on clinician referral such as lack of time during consultations; knowledge about ERS, views on evaluation; and medico- legal responsibility [42,67-69].

